### 2.9. Confidentiality and Concealment

Each user will receive unique login credentials, which will be distributed according to the study’s Signature and Delegation Log to ensure proper access control. The randomisation and allocation process will be fully automated to prevent any researcher involvement in participant assignment. The allocation sequence will be concealed and only revealed to the clinical team at the time of participant assignment.

## 3. Blinding

Although it will not be possible to blind the allocation to study arms due to the nature of the PGT-A strategy and the regulatory requirements of the Human Fertilisation and Embryology Act 1990 and the Human Fertilisation and Embryology Code of Practice 2009—which mandate that couples are informed about the fate of their embryos (whether subjected to PGT-A or not)—we will implement several strategies to minimise potential bias from both researchers and participants.

Data analysts will be blinded to participant allocation, ensuring that the interpretation of results remains impartial and unaffected by knowledge of group assignments. All study procedures, including data collection and outcome assessment, will be standardised to minimise variability and reduce bias. Comprehensive training will be provided to all staff to ensure the consistent application of protocols across all study sites.

Regular audits and reviews will be conducted to ensure adherence to protocols and to identify and address any sources of bias. Wherever feasible, outcome assessors will be blinded to participant allocation to prevent their knowledge of the group assignments from influencing the evaluation of the outcomes. Robust measures will be implemented to secure participant data and maintain confidentiality, with access to sensitive information restricted to authorised personnel only, further reducing the risk of bias.

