### 2.8. Minimisation Algorithm

The randomisation system (allocation ratio 1:1) will employ a minimisation algorithm to ensure balance across the following factors: IVF clinic, female age (35–37, 38–39 and 40–42 years), BMI (20–<25, 25–<30, ≥30), previous live birth, type of ovarian stimulation protocol (gonadotrophin-releasing hormone (GnRH) agonist or GnRH antagonist; human chorionic gonadotrophin (hCG) or GnRH agonist trigger), and standard IVF or ICSI.

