### 6.3. Care Pathway Post-Randomisation

Women in the control arm will proceed with a fresh embryo transfer procedure on day 5 following egg collection, or, if clinically indicated, a frozen–thawed embryo transfer as first-line treatment over a fresh transfer. Women in the experimental arm will have PGT-A performed from trophectoderm biopsy on embryos that reach the blastocyst stage, which typically occurs on days 5, 6, or 7 following egg collection.

All embryos will be frozen after the biopsy procedure. The CCS of all chromosomes will be performed using NGS and embryos will be categorised as euploid, mosaic aneuploid, and aneuploid embryos. Mosaic embryos will be ranked based on the degree of aneuploidy (low- and high-mosaic aneuploid embryos).

A low-mosaic embryo is defined as an embryo with whole-chromosome aneuploidies in 30–50% of the biopsied cell and a high-mosaic embryo is defined as an embryo with whole-chromosome aneuploidies in 50–70% of the biopsied cells.

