### 6.4. Embryo Transfer

Only single-euploid embryos or low-mosaic embryos that are deemed suitable to be replaced, with prioritisation based on the morphological grading of the embryos, will be transferred in subsequent frozen–thawed embryo transfer cycles, which could be initiated as early as with the next menstrual cycle following egg collection. Euploid embryos will preferably be transferred to low-mosaic embryos and the couple will need to undergo genetic counselling before transferring a low-mosaic embryo.

The subsequent frozen–thawed embryo transfer (FET) of a single-euploid embryo will occur either in a natural cycle or a hormonally medicated cycle using physiological doses of oestrogen and progestogens to prepare the endometrium.

If patients decide not to transfer mosaic embryos, these instances will be thoroughly documented, including the reasons and clinical factors involved. These data will be incorporated into the study through descriptive analysis, which will outline the frequency of and reasons for these decisions. Additionally, sensitivity analyses will assess how excluding mosaic embryos affects the study outcomes, ensuring that the results accurately reflect both the protocol and real-world practices. The final report will address the implications of transferring versus not transferring mosaic embryos on the study’s primary and secondary endpoints, providing a comprehensive understanding of their impact.

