## 7. Preliminary Results

If the preliminary results show promising trends and outcomes consistent with the study hypotheses, and statistical analyses (including Bayesian methods if applicable) indicate the potential for meaningful findings, the study will continue. If the preliminary results are inconclusive or show no evidence of potential benefit, or if analyses indicate that the study objectives are unlikely to be met, the study will be reassessed. Decisions will be made based on the overall value of continuing versus terminating, considering the insights from the preliminary analyses.

To analyse of our outcomes of interest, logistic regression or linear mixed models, as well as survival analyses or chi-square tests, will be used.

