### 7.2. Handling Participants Who Do Not Follow Their Allocated Arm

Participants who do not adhere to their allocated study arm will be tracked through the study’s monitoring system. Reasons for non-compliance will be documented, and alternative approaches will be considered to account for deviations in the final analysis. Non-compliance will also be recorded and assessed to understand its impact on study outcomes. The analysis will include intention-to-treat (ITT) and per-protocol approaches to evaluate the effect of treatment allocation versus the actual received treatment.

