### 7.3. Recording and Assessing PGT-A Arm with No Embryos to Biopsy

For participants randomised to the PGT-A arm who have no embryos available for biopsy, detailed documentation will be maintained. This will include the reasons for the absence of viable embryos, such as poor ovarian response or embryo quality issues. These cases will be assessed and recorded as deviations from the intended intervention. The impact of such deviations on the study outcomes will be analysed, and the data will be included in the final study report to provide a comprehensive view of the feasibility and practical challenges of PGT-A’s implementation.

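### Section 3 claims analyst blinding without limit, but several planned analyses, among them the mosaic and no-biopsy analyses, cannot be done blind

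*Protocol article*

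**What the plan says.** Section 3 explains that allocation cannot be hidden from participants and clinicians, and then lists measures against bias. The one for analysts is absolute: "Data analysts will be blinded to participant allocation, ensuring that the interpretation of results remains impartial and unaffected by knowledge of group assignments". The one for outcome assessors, in the same section, is conditional: "Wherever feasible, outcome assessors will be blinded to participant allocation".

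Other sections describe data and analyses that bear on this claim:

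- Section 6.3, on the PGT-A arm: "All embryos will be frozen after the biopsy procedure". Control women have a fresh transfer on day 5 by default, or a frozen one where clinically indicated.
- Section 6.4, on mosaic embryos, plans a description of how often and why couples decline them, and adds that "sensitivity analyses will assess how excluding mosaic embryos affects the study outcomes".
- Section 7.2: "The analysis will include intention-to-treat (ITT) and per-protocol approaches to evaluate the effect of treatment allocation versus the actual received treatment".
- Section 7.3, on women allocated to PGT-A who have nothing to biopsy: "The impact of such deviations on the study outcomes will be analysed".
- Sections 2.1 and 4 make adherence, including adherence to the allocated arm, part of what the pilot measures.

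**The concern.** Coded arm labels blind an analyst only while the rest of the file does not reveal the code. Ploidy class, mosaic status and the no-biopsy flag are recorded for one arm only. An analyst who opens any of these fields can tell which code is PGT-A. The safeguard is stated for all analysis, yet the protocol plans analyses that need exactly these fields.

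What is at stake is an accurate description of bias protection in an open trial. It matters somewhat beyond the pilot: Section 2.1 intends the pilot results to enter the main trial, and Section 7 makes continuation depend partly on preliminary results. If analysts learn the arms before the comparative analysis is settled, that knowledge carries forward.

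**Working it through.** The plan gives no figure on this point, so there is none to reproduce and no formula applies. The check lists the planned analyses and asks what data each needs. An analysis is classed as revealing if it needs a field that exists in one arm only, or that is defined by allocation or treatment received. It is classed as possibly revealing if only the pattern of values could identify the arm.

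| Planned analysis | Section | Data needed | Reveals the arm? |
|---|---|---|---|
| Recruitment | 4, 6.9 | no arm | no |
| Randomisation | 4 | no arm | no |
| Baseline comparison | 6.8 | arm code, pre-treatment variables | no |
| Clinical pregnancy per randomised woman, intention-to-treat | 5, 7.2 | arm code, outcome | no |
| Clinical pregnancy per transferred embryo | 5 | arm code, transfer count, outcome | no |
| Miscarriage per transferred embryo | 5 | arm code, transfer count, outcome | no |
| Time to pregnancy leading to live birth | 5 | arm code, duration | possibly, by pattern |
| Adherence to allocated arm | 2.1, 4, 7.2 | allocation and treatment received | yes |
| Per-protocol | 7.2 | allocation and treatment received | yes |
| Mosaic, descriptive | 6.4 | ploidy results | yes |
| Mosaic, sensitivity | 6.4 | ploidy results | yes |
| No embryo to biopsy | 7.3 | group defined within the PGT-A arm | yes |

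Result: 5 + 1 + 6 = 12. Five of 12 (42%) reveal the arm, or six of 12 (50%) if time to pregnancy is added. A different grouping would shift these counts slightly.

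Two rows need comment.

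- **Time to pregnancy.** It needs no arm-specific field. But PGT-A transfers are all frozen and start at the earliest in the menstrual cycle after egg collection (Sections 6.3 and 6.4), while control transfers are by default fresh on day 5. The coded arm with the later times is therefore probably PGT-A. Some control transfers may be frozen, so this is a likelihood and not a certainty.
- **Per-embryo rates.** They need a count of transfers, not their date or type. A fresh transfer would identify a control woman, but a frozen one would not identify a PGT-A woman, and neither field is needed for these rates.

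Arm size gives nothing away: "The randomisation system (allocation ratio 1:1) will employ a minimisation algorithm".

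**The case against.** The strongest reply is that blinding is available where it counts most. Analysts could finish the intention-to-treat comparisons on coded arms before they receive ploidy or biopsy data, and another person could derive the per-protocol flag. Section 3 restricts access to sensitive information, and nothing in the article says that analysts receive the revealing fields early. Arm coding, masking and the order of analyses commonly sit in a full protocol or statistical analysis plan, which is not shown.

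Most of this stands. The absence of a described mechanism is not an error in the article. What does not fall to the reply is the breadth of the sentence: even with ideal sequencing, whoever runs the mosaic and no-biopsy analyses knows the arm, and an unlimited claim is untrue for them.

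A reader might infer more than the documents support:

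- **That most analyses are unblindable, or that the safeguard is empty.** The count above is at most half, and the main between-arm comparison can be masked.
- **That only one of the four secondary outcomes can be analysed blind.** None of the four needs an arm-specific field, and only time to pregnancy is exposed, by its pattern.
- **That an unblinded analyst is left free to pick the test.** Section 7 does list alternatives: "To analyse of our outcomes of interest, logistic regression or linear mixed models, as well as survival analyses or chi-square tests, will be used". But Section 6.9 says that the tests will be specified, and fixing them is ordinary analysis-plan content.
- **That the false-positive rate rises by a known amount.** The documents give no basis for such a figure. Section 7.2 plans both intention-to-treat and per-protocol analyses and does not say that the more favourable one will be chosen. Section 6.9 also promises correction for multiple comparisons.
- **That Section 7 has blinded analysts judging whether results favour PGT-A.** It does not say who decides, and others could unmask after a coded analysis.

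**Conclusion.** The point holds in limited form. The analyst-blinding statement in Section 3 is too broad. It cannot be true of the mosaic descriptive and sensitivity analyses, the per-protocol analysis by treatment received, the no-biopsy analysis or arm adherence, and it is doubtful for time to pregnancy. It can be true of the intention-to-treat comparison of clinical pregnancy per randomised woman and of the per-embryo pregnancy and miscarriage rates.

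This assumes that the same analysts handle the revealing fields. If a separate person derives a simple per-protocol flag, that one analysis could be partly masked. The mosaic and no-biopsy analyses could not.

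Severity is minor. The primary outcome is feasibility, the recruitment threshold of 60 women out of 100 in 18 months is not a between-arm comparison, and Section 6.7 says that hypothesis testing is not the main focus.

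**What to change.** Reword Section 3 so that analyst blinding is claimed only for the intention-to-treat comparisons on coded arms. Support it with a two-step order of work:

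1. Fix the method for each endpoint. Run the coded comparisons on a file without biopsy, ploidy, fresh/frozen and transfer-date fields. Run time to pregnancy only from code locked beforehand.
2. Then release the remaining fields, and report the per-protocol, mosaic, no-biopsy and arm-adherence analyses as unblinded.

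The cost is a change of wording and one extra data extract. The downside is that the blinding must be described as partial.

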## 4. Primary End Point

Our primary outcome of interest will be the ability to recruit, randomise, and ensure adherence to the study protocol to plan the full study.

## 5. Secondary End Points

The following secondary outcomes will be recorded:Clinical pregnancy rate per transferred embryo.Clinical pregnancy rate per randomised woman.Miscarriage rate per transferred embryo.Time to pregnancy leading to live birth.

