## 1. Introduction

### 1.1. Background

The selection of the most viable embryo is typically based solely on light microscopy and morphological assessment in assisted reproductive technologies (ART) [1,2,3]. However, despite significant technological and scientific advances in the field, many women still fail to achieve clinical pregnancy or live birth, despite the transfer of embryos classified as good quality by various guidelines [4,5,6,7,8]. This high rate of failure is believed to due to the limitations of relying solely on morphological evaluation, which is an inefficient method of determining embryo ploidy, unable to accurately distinguish between euploid, aneuploid, or mosaic embryos, which have distinct implantation potentials [3,7,8]. The human embryo aneuploidy rate is reported to range between 30% and 50% when under 35 years of age and to increase to 80% in patients aged 42 years of age or older [9,10], reflecting the higher miscarriage rates and lower live birth rates often seen in women of advanced reproductive age. Often, to increase the chances of a live birth, assisted-conception units rely on the transfer of multiple embryos graded as good on morphological criteria alone. However, multiple-embryo transfer is known to increase the risk of multiple pregnancies, which are associated with significant foetal, maternal, and neonatal risks, as well as long-term complications [11]. In view of this, providing patients with an added level of single-embryo selection beyond a static or dynamic morphologic evaluation is of increasing clinical importance.

Preimplantation genetic testing for aneuploidies (PGT-A), combined with next-generation sequencing (NGS), aims to identify and transfer euploid embryos with the highest implantation potential, while excluding aneuploid embryos that are likely to arrest in development and lead to negative pregnancy outcomes [12,13,14]. In additional to shortening the time-to-pregnancy timeline, reducing the miscarriage rate, and improving live birth rates, IVF with PGT-A also aims to promote single-embryo transfer, thereby reducing the risk of multiple births without lowering overall IVF success rates [13,15].

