### 6.2. Timing of Randomisation

Randomisation will occur on day 3 following egg collection. At this point, all consented patients will be evaluated for eligibility. Specifically, patients will be randomised if they have at least three good-quality embryos, as assessed using the embryo-scoring system of the Association of Clinical Embryologists (UK).

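### Pregnancy and miscarriage per transferred embryo use a denominator that PGT-A itself shrinks, so they are not randomised comparisons, and miscarriage has no per-woman version

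*Protocol article*

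**What the plan says.** Section 5 of the protocol article lists four secondary endpoints. Pregnancy appears twice, as "Clinical pregnancy rate per transferred embryo" and as "Clinical pregnancy rate per randomised woman". Miscarriage appears once, as "Miscarriage rate per transferred embryo".

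The order of events matters:

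- Section 6.2: "Randomisation will occur on day 3 following egg collection". Biopsy and transfer come later.
- Section 6.3: "Women in the control arm will proceed with a fresh embryo transfer procedure on day 5 following egg collection", or has a frozen transfer if clinically indicated. This arm has no ploidy filter, and the text does not say how many embryos are transferred.
- Section 6.4, PGT-A arm: "Only single-euploid embryos or low-mosaic embryos that are deemed suitable to be replaced" may be transferred.
- Section 7.3 foresees PGT-A women with nothing to biopsy.
- Section 7.2 promises both intention-to-treat and per-protocol analyses.

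For mosaic embryos, section 6.4 adds that "sensitivity analyses will assess how excluding mosaic embryos affects the study outcomes".

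**The concern.** A PGT-A woman whose embryos all fail the ploidy filter contributes no embryo to a per-embryo rate. Her counterpart in the control arm is transferred and counted. The two denominators therefore describe differently selected women, and the selection is made by the intervention under study. No choice of statistical test restores the comparison that randomisation set up.

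Pregnancy has a safeguard, because the per-randomised-woman rate is in the same list. Miscarriage has none. The only miscarriage endpoint omits every randomised woman without a transfer, so as listed it has no intention-to-treat form.

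These are secondary endpoints of a feasibility pilot, but they will be used. Section 6.8 promises a full trial analysis, and section 6.9 foresees tests of secondary outcomes. Section 7 links continuation to how the early outcomes look. Section 2.1 intends to carry the pilot data into the main trial, whose purpose includes both effectiveness and safety.

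**Working it through.** The protocol gives no numerical figure for these endpoints, so there is none to reproduce. The check is ratio arithmetic.

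**Inputs**

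- From section 1.1: embryo aneuploidy of 30–50% under 35 years, rising to 80% at 42 or older.
- From sections 6.7 and 2.8: 100 women at 1:1, so about 50 per arm.
- Assumed, because the document gives no values: in the control arm, 30% clinical pregnancy per randomised woman; 30% of pregnancies miscarry, so 0.30 × 0.30 = 9% miscarriage per woman; one embryo per transfer and one transfer per woman.
- *s* is the number of embryos transferred per PGT-A woman relative to control.

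**Step 1: how far *s* may fall.** Take embryo results as independent and ignore mosaics. At 50% aneuploidy, all of three biopsied blastocysts are aneuploid with probability 0.5³ = 12.5%, and both of two with probability 0.5² = 25%. This gives *s* = 0.875 and 0.75. These are illustrations, not forecasts.

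**Step 2: no effect per woman.** If the rate per randomised woman is *r* in both arms, the PGT-A per-embryo rate is *r*/*s*.

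| | Control | PGT-A, *s* = 0.875 | PGT-A, *s* = 0.75 |
|---|---|---|---|
| Pregnancy per woman | 30% | 30% | 30% |
| Pregnancy per embryo | 30% | 0.30/0.875 = 34% | 0.30/0.75 = 40% |
| Miscarriage per woman | 9% | 9% | 9% |
| Miscarriage per embryo | 9% | 0.09/0.875 = 10.3% | 0.09/0.75 = 12% |

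Pregnancy per embryo falsely favours PGT-A. Miscarriage per embryo falsely counts against it.

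**Step 3: implantation falls.** Let pregnancy per embryo drop from 30% to 20%, with 30% of pregnancies still miscarrying. Miscarriage per embryo goes from 0.30 × 0.30 = 9% to 0.30 × 0.20 = 6%. A loss of pregnancies now looks like a safety gain.

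**Step 4: the test is uninformative.** Let 25% of PGT-A women lose their transfer at random, with 30% pregnancy per transferred embryo in both arms.

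- Pregnancy per embryo: 30% in both arms. Per woman: 30% against 0.75 × 30% = 22.5%.
- Miscarriage per embryo: 9% in both arms. Per woman: 9% against 0.75 × 9% = 6.75%.
- Miscarriage per clinical pregnancy: 30% in both arms.

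The embryo denominator hides the loss of pregnancies. Miscarriage per woman also falls, simply because fewer women conceive, so it cannot be read alone.

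**Step 5: effect on a test.** With 50 women per arm, an assumed 35% pregnancy per woman in both arms, and a two-sided 5% test of 50 against 50*s* embryos (normal approximation), the per-embryo pregnancy comparison rejects about 6% of the time at *s* = 0.9, 28% at *s* = 0.7 (35% against 0.35/0.7 = 50%) and 83% at *s* = 0.5.

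**The case against.** **Feasibility pilot.** The primary outcome is feasibility (section 4), section 2 disclaims firm conclusions on pregnancy, and pregnancy per randomised woman is already listed. This stands and limits the harm for pregnancy. It does not help miscarriage, which has one denominator only.

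**Direction.** A reader might infer that both per-embryo endpoints flatter PGT-A when there is no effect. That holds for pregnancy only. Miscarriage is an adverse event, so equal events over fewer embryos raise the PGT-A rate (step 2).

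**The per-woman miscarriage rate has a weakness too.** It also falls when fewer women conceive (step 4). This is correct, so it has to be read beside pregnancy per randomised woman.

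**Size.** With the 80% aneuploidy figure, 0.8³ = 51% of women would have no transferable embryo, and 30% would become 0.30/0.488 = 61%. That is an extreme corner. The figure is quoted for age 42 and older while the trial enrols ages 35–42; three good embryos on day 3 is a minimum and does not fix the number of blastocysts; and low-mosaic embryos may be transferred. Section 9 also describes a ranking that runs on to high-mosaic and aneuploid embryos. It must be reconciled with section 6.4, which the working follows.

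**Two-embryo control transfers.** A reader might infer that these deflate the control per-embryo rate, since section 1.1 says that "assisted-conception units rely on the transfer of multiple embryos graded as good on morphological criteria alone". That sentence is background on general practice, not a rule for the control arm. Section 6.3 sets no number, so no size can be given.

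**Mosaic sensitivity analysis.** Section 6.4 does not say that the woman leaves the denominator, and such detail may sit in an analysis plan. What stands is that mosaic status is known only in the tested arm, so excluding mosaic embryos can alter only that arm.

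**Conclusion.** The point holds in a limited form. Both per-transferred-embryo rates use a denominator that arises after randomisation and that the PGT-A filter changes. They are not randomised comparisons and cannot serve as the intention-to-treat analysis of section 7.2.

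With equal per-woman rates, per-embryo pregnancy is multiplied by 1/*s* in favour of PGT-A: a gain of about 4 to 10 percentage points on a 30% base for 12.5% to 25% of PGT-A women without transfer. The base rate and these shares are assumptions. For miscarriage the direction is not fixed, and no intention-to-treat version is listed. That is the more serious gap, because safety is among the aims of the trial that will absorb these data. The plan should be changed, but the pilot's feasibility outcome is not affected.

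**What to change.** 1. In section 5, name clinical pregnancy per randomised woman as the lead clinical comparison.
2. Add miscarriage per randomised woman, with the instruction that it is always reported beside pregnancy per randomised woman. Give miscarriage per clinical pregnancy as supporting description; its denominator also arises after randomisation.
3. Keep the per-transferred-embryo rates, labelled as descriptive and not as evidence of a treatment effect.
4. In section 6.4, state that the mosaic sensitivity analysis keeps all randomised women in the denominator, and how the outcome of a woman with a mosaic transfer is then counted.

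The cost is wording only. Pregnancies, miscarriages, transfers and randomised women are recorded in any case. The downside is that the reported PGT-A pregnancy rate will look less favourable than the per-embryo figure.
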